## Abstract

**Background:**

Despite the benefits of physical activity for walking ability, balance, and mood, less than 30% of stroke survivors engage in recommended levels of physical activity with high levels of sedentary behaviour observed. This study aims to assess the feasibility, acceptability and fidelity of a theory- and evidence-based multifaceted behaviour change intervention targeting free-living physical activity and sedentary behaviour after stroke.

**Methods:**

This study will be set in community stroke services in the North East of England and will assess the feasibility of a behaviour change intervention targeting free-living physical activity and sedentary behaviour of stroke survivors *and* consultation behaviour of the healthcare professionals to support stroke survivors to make these lifestyle changes. Up to 35 stroke survivors currently receiving stroke rehabilitation within the study catchment area with capacity *and* no contraindications to increasing physical activity/reducing sedentary behaviour will be recruited. Stroke survivors will receive a supported self-management physical activity/sedentary behaviour programme incorporating provision of information, goal setting, action planning, barrier identification, coping planning, self-monitoring and feedback on physical activity and sedentary behaviour. The programme will be supported by up to 12 healthcare professionals (HCPs) recruited from the community stroke services taking part in the study. The HCPs will deliver at least two face-to-face sessions (baseline, review and subsequent reviews if necessary) and provide a range of personalised tools to support each individual stroke survivor (e.g. workbook, self-monitoring tools, information on local resources). The consultation behaviour of the HCPs will be targeted via a training programme incorporating face-to-face training, a training manual and individual feedback on intervention programme delivery from the study research team. The feasibility, acceptability and fidelity of the study protocol will be assessed.

**Discussion:**

The most effective methods of supporting stroke survivors to alter physical activity and sedentary behaviour have yet to be established. This study will establish the feasibility of delivering a complex theory- and evidence-based intervention targeting the behaviour of both stroke survivors and HCPs and assess whether it is acceptable to the target populations. Findings will inform the iterative development of the intervention before a larger scale evaluation.

**Trial registration:**

Trial register: Trial identifier: ISRCTN35516780, date of registration: 24/10/2018

## Background

Increasing physical activity levels and reducing sedentary behaviour (e.g. the time spent sitting or lying) can improve health outcomes and reduce mortality [1, 2]. Home and community physical activity levels are consistently low after stroke, with stroke survivors spending the majority of their day either sitting or lying down [3, 4]. Numerous barriers to engagement in physical activity have been cited after stroke including stroke-related impairments, lack of professional support, reduced self-efficacy and cost and access to facilities [5, 6]. These complex barriers may account for the low levels of physical activity observed after stroke and explain why at present the most effective methods of engaging stroke survivors in long-term free-living physical activity and reducing sedentary behaviour have yet to be ascertained.

Structured exercise is one method of increasing physical activity and has been shown to lead to short-term improvements in walking performance [7], physical fitness [8], metabolic risk factors [9] and mood and quality of life [10]. These short-term benefits however do not appear to be sustained, and the predominant mode of delivery of structured exercise (face-to-face group work) presents with numerous barriers to engagement including access, cost, sustainability and transport. Arguably, the lack of long-term benefit of structured exercise is due to a lack of emphasis on ‘free-living’ behaviour and self-management during this mode of delivery. This argument is supported by previous research findings indicating structured exercise sessions may only improve free-living physical activity levels if delivered alongside tailored counselling (e.g. group/individual counselling strategies including goal setting, monitoring and review) [11]. Interventions that promote supported self-management, e.g. where individuals are provided with the information and skills to effectively manage their long-term condition, can improve long-term outcomes after stroke [12]. Supported self-management may therefore be a useful mode of delivery for an intervention promoting physical activity and sedentary behaviour change after stroke. A number of small feasibility studies have indeed demonstrated that supported self-management is feasible for targeting physical activity/sedentary behaviour after stroke [13, 14].

It is argued that interventions that target behaviour change should have a strong theoretical background to promote change and increase understanding of the determinants of that change. Although complex interventions, few of the existing physical activities and other lifestyle interventions tested post-stroke are based on theory or developed using frameworks [15, 16], which may be why minimal effects have been observed. Interventions based on behaviour change theory in other long-term conditions such as rheumatoid arthritis and lower back pain have shown improvements in long-term physical activity [17, 18]. There is a dearth, however, of research of this type in stroke. Use of theory and frameworks to develop interventions to target physical activity and sedentary behaviour after stroke may lead to an increased likelihood of improving long-term behaviour.

### Intervention development

#### Stroke survivor component

Results of a systematic review and in-depth qualitative study conducted by our study team, and usability/acceptability testing of prototypes of components of the intervention, have been used to develop the content of the stroke survivor intervention.

We have conducted a systematic review of the literature on interventions targeting long-term physical activity and sedentary behaviour following stroke [19]. Intervention study components were established using the Template for Intervention Description and Replication (TIDieR) framework [20] and the Behaviour Change Taxonomy V1 [21]. Nine interventions targeting physical activity were identified by the review, and six of those were rated as very/quite promising. No interventions were identified targeting sedentary behaviour. Face-to-face and telephone supervised support were rated as promising modes of delivery. Intensity of support provided did not alter intervention promise. Behaviour change techniques (BCTs) identified as promising were action planning, goal setting behaviour, problem solving, biofeedback, feedback on behaviour, credible source, social support, information about health consequences and information about social-environmental consequences. Only two of the interventions identified from the included studies were theory-based.

Alongside the review, an in-depth qualitative study has been conducted [22]. The qualitative study identified the barriers and enablers to participation in physical activity and reducing sedentary behaviour after stroke from the perspective of stroke survivors, informal carers and healthcare professionals (see healthcare professional intervention development below). The findings were thematically analysed using the Theoretical Domains Framework (TDF) [23], and this framework was used to map emergent behaviour change techniques and theory related to the behaviour of the stroke survivors. Five major themes were identified that were linked to both consultation behaviour of healthcare professionals supporting stroke survivors to increase physical activity and reduce sedentary behaviour after stroke and the views identified by the stroke survivors and informal carers. These themes were education/training, information provision, daily activities, resources and confidence.

Findings of the systematic review and the qualitative study, alongside an assessment of the community team’s resources, were combined to provisionally map the content of the current stroke survivor intervention, in terms of theoretical domains and constructs, behaviour change techniques and intervention components. Following this provisional mapping exercise, feedback on acceptability and usability of the intervention and intervention tools was gathered from a series of workshops/interviews/questionnaires with stroke survivor and informal carers and healthcare professionals (HCPs). The intervention components were iteratively developed based upon this feedback to finalise the intervention for this study. The development of the intervention will be described in full in a separate publication.

#### Healthcare professional training (HCP) programme

The content of the HCP training programme has been developed in part from our qualitative study where we investigated the perceived barriers and enablers to HCPs supporting people with stroke to increase physical activity and reduce sedentary behaviour. The study identified the following BCTs likely to target the behaviour of the HCPs: problem solving, action planning, monitoring of outcomes of behaviour without feedback, social support (practical), social support (emotional), instruction on how to perform a behaviour, information about health consequences, salience of consequences, demonstration of behaviour and credible source. These BCTs have been incorporated into the HCP training programme which is underpinned by Social Cognitive Theory [24]. The training programme was piloted on a group of HCPs who will not be involved in the study to determine appropriate content and mode of delivery.

### Aim

The overall aim of this study is to assess the feasibility, acceptability and fidelity of a theory- and evidence-based multifaceted behaviour change intervention targeting free-living physical activity and sedentary behaviour after stroke.

#### Objectives

To determine stroke survivor and HCP study recruitment and attrition ratesTo report feasibility of intervention delivery (mode, delivery time, application of intervention components, safety)To report completeness of baseline and review descriptive data to determine the feasibility of the inclusion criteria and of potential outcome measuresTo obtain views of stroke survivors on the acceptability of the intervention and study protocolTo assess the fidelity of delivery, receipt and enactment of the interventionTo assess the reaction, attitudes and skills of the HCPs pre and post training programmeTo assess the cognitive and behavioural skills of the HCPs in response to training programme

## Methods

### Study setting

The study will be set in NHS community stroke services in the North East of England (a list of study sites is available at http://www.isrctn.com/ISRCTN35516780).

### Study design

This is a multi-centre feasibility and acceptability study. The multifaceted behaviour change intervention will target both the free-living physical activity and sedentary behaviour of stroke survivors, and the consultation behaviour of the healthcare professionals supporting stroke survivors to target these behaviours.

#### Progression criteria

Progression criteria to the next stage of the study have been developed in accordance to the traffic light system described by Avery et al. [25]:

Green—Progression to the next stage of the study is appropriate without alteration to the protocol

Amber—Progression to the next stage of the study is appropriate with iterative changes to the protocol

Red—Progression to the next stage of the study is not appropriate

Progression criteria:
Green—The proposed sample size is achieved and retained, the intervention is considered acceptable and feasible by healthcare professionals, stroke survivors with only minor changes are required (e.g. minor changes to written information content), the study procedures are considered acceptable and feasible and at least 85% of outcome data is collected (i.e. case report form and questionnaire completion).Amber—At least 14 stroke survivors (based upon recommendations made by Julios et al. [38]) and at least 7 healthcare professionals were recruited and retained at follow-up, moderate changes to the intervention are required (e.g. additional time required to deliver review sessions or additional intervention content is required), moderate changes to the protocol are required (e.g. amendments to recruitment strategy and data collection procedures) and a minimum of 60% of outcome data is collected.Red—< 14 stroke survivors and < 7 healthcare professionals were recruited and retained at follow-up, significant changes to the intervention are required (e.g. change in mode of delivery, frequency of sessions and content of intervention), significant changes to the protocol are required (e.g. eligibility criteria in order to achieve sample size, alternative data collection tools/instruments) and < 60% of outcome data was collected.

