### Sample size

We aim to recruit and retain up to 35 stroke survivors (in line with standard guidance for feasibility studies [26]). As this is a feasibility study, a formal sample size calculation has not been undertaken. The sample size has been selected to allow adequate testing of the intervention and has been based on local resources. We aim to recruit up to 12 HCPs to take part in the training programme and intervention delivery. This sample size has been decided upon based on feedback from study sites.

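### Red joins its progression criteria with 'and', so it is not the complement of Amber and Green, and many mixed results receive no grade

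*Protocol article*

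**What the plan says.** The section Progression criteria in the protocol article (Methods, Study design) defines three grades, each as one sentence with its items separated by commas and a closing 'and'.

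- **Green:** "The proposed sample size is achieved and retained", the intervention is acceptable and feasible with only minor changes, and "the study procedures are considered acceptable and feasible and at least 85% of outcome data is collected".
- **Amber:** "At least 14 stroke survivors" and at least 7 HCPs recruited and retained, moderate changes to the intervention, moderate changes to the protocol, "and a minimum of 60% of outcome data is collected".
- **Red:** "< 14 stroke survivors and < 7 healthcare professionals were recruited and retained at follow-up", significant changes to the intervention, significant changes to the protocol, and less than 60% of outcome data.

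The targets behind Green are in Sample size: "We aim to recruit and retain up to 35 stroke survivors" and "We aim to recruit up to 12 HCPs".

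Nothing in the article says how a mixed result is graded, whether one Red item is enough, or whether the worst item decides. The Aim is to "assess the feasibility, acceptability and fidelity of a theory- and evidence-based multifaceted behaviour change intervention", and Objective 5 is about fidelity, but no grade names fidelity.

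**The concern.** A traffic-light rule should give every possible result exactly one colour. The opposite of 'at least 14 and at least 7' is 'fewer than 14 or fewer than 7'. Red is written with 'and', both between the two counts and across the remaining items. A study that misses some of the Amber minimums, but not all of them, therefore falls outside Amber without falling into Red.

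The grade decides whether the next stage goes ahead unchanged, goes ahead with changes, or does not go ahead. Where the rule is silent, the team would have to choose the grade with the results in view, and that is what criteria set in advance are meant to prevent.

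**Working it through.** The plan states no figure that could be reproduced here, and Sample size says that no formal calculation was made. The check is to apply the rule as written.

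**Inputs (Progression criteria; Sample size).** Five items: survivors retained (Red below 14, Amber from 14, Green 35), HCPs retained (Red below 7, Amber from 7, Green 12), intervention changes (significant, moderate, minor), protocol changes (significant, moderate, acceptable as they are), outcome data (below 60%, from 60%, from 85%). The 'up to' figures are read as the Green targets.

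**Single results tested against each grade**

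- 10 survivors, 8 HCPs: not Red, because 8 is not below 7; not Amber, because 10 is below 14; not Green.
- 30 survivors, 10 HCPs, 45% of data: not Red, because neither count is low; not Amber, because 45% is below 60%; not Green.
- 5 survivors, 7 HCPs, significant changes to both intervention and protocol, 30% of data: not Red, only because 7 is not below 7; not Amber; not Green.

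**All combinations.** Five items at three levels give 3^5 = 243 profiles.

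- Green, all items Green: 1.
- Red, all items Red: 1.
- Amber, read leniently as every item at Amber or better but not all Green: 2^5 − 1 = 31.
- Ungraded: 243 − 1 − 1 − 31 = 210, and 210/243 = 86%.
- Profiles with at least one Red item: 243 − 2^5 = 211, of which 1 is graded Red.

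**Sensitivity to the reading**

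- Amber read literally, with exactly moderate changes on both change items: 2 × 2 × 1 × 1 × 2 = 8 Amber profiles, and 243 − 1 − 1 − 8 = 233 ungraded (96%).
- Green without an HCP target: 209 ungraded (lenient Amber) or 231 (literal Amber).
- Only the three numeric items: 3^3 = 27 profiles, with 1 Green, 2^3 − 1 = 7 Amber, 1 Red and 18 ungraded (67%).

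**Recruitment counts alone.** Survivors 0 to 35 by HCPs 0 to 12 give 36 × 13 = 468 cells. The Red counts cover 14 × 7 = 98, the Amber-or-better counts cover 22 × 6 = 132, and 468 − 98 − 132 = 238 (51%) meet neither.

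**After the repair.** With Green for all Green, Red for any Red and Amber for the rest, the 243 profiles divide into 1 Green, 31 Amber and 211 Red, with none ungraded.

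**The case against.** The best defence is that the grades can be read item by item. Their numeric cut-offs are complementary (14, 7 and 60%), so no single numeric item has a gap between Amber and Red, and a sensible team would take any Red item as Red. This stands in part: only the combining rule is defective, and a short rewording cures it. But the text does not state the 'any' rule, and the explicit 'and' between the two Red counts points the other way.

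Some stronger readings are tempting but not supported:

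- A reader might take 86% as the chance of an ungraded study, or conclude that the rule fails in the likeliest situations. The figure counts profiles equally. The items are linked in practice: the section's own examples tie a recruitment shortfall to changes in recruitment strategy or eligibility. The documents give no basis for probabilities.
- A reader might infer that safety is outside the rule and that poor delivery would pass as Green. Objective 2 places safety and the application of intervention components under feasibility of delivery, and Green requires a feasible intervention. Poor delivery that called for new content, frequency or mode would also count under the intervention-change item. What remains is narrower: no grade names fidelity or sets a threshold for it.
- A reader might call the progression decision the study's main product. The Aim is to assess feasibility, acceptability and fidelity, and the abstract says that the findings feed iterative development of the intervention.

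It is also fair that two of the five items, moderate and significant changes, need judgement after the results under any wording.

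**Conclusion.** The point holds as an error in the stated decision rule. Red, as worded, needs every item to fail together, and Amber needs all its minimums, so results between them have no grade. One realistic ungraded result, such as 10 survivors with 8 HCPs, is enough to show this. The size, 210 of 243 profiles on the lenient reading of Amber, is a logical count that rests on five items at three levels and on 35 and 12 as the Green targets. Other readings move the count between 209 and 233 and leave the conclusion unchanged. No estimate of recruitment, retention, completeness or fidelity is affected; only the grading is.

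**What to change.** Before data are seen, reword the paragraph:

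- In Red, replace 'and' by 'or': at the least, fewer than 14 survivors or fewer than 7 HCPs, or less than 60% of outcome data.
- State the combining rule: Green if all items are Green; Red if any item is in its Red range, or any of a named set that the team regards as decisive alone; Amber for everything else. Every result then has exactly one grade.

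The rewording needs no extra data. Its cost is that Red becomes considerably easier to reach: under the 'any' rule it goes from 1 to 211 of the 243 profiles, and a study with 35 survivors, 12 HCPs and 59% of data would be Red. If the team finds that too strict, naming the decisive items is the way to soften it.

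Optional: because fidelity is in the Aim and is Objective 5, the team may add a fidelity-of-delivery criterion. The coding of behaviour change techniques planned under Objective 7 would supply the data, but cut-offs would have to be chosen before the recordings are coded. This is a design preference and not part of the error.

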#### Stroke survivor eligibility criteria

Inclusion criteria:
Adult community dwelling stroke survivorsCurrently receiving outpatient/community stroke rehabilitation in the study catchment areaCapacity to provide informed consent and capability to undertake a supported self-management physical activity intervention programme (e.g. not requiring high levels of hands on therapy for function).Agreement by the therapist and patient that there is capacity for increased activity / less sedentary behaviour

Exclusion criteria:
Contraindications for undertaking physical activity e.g. presence of unstable heart diseaseAdvised by GP/Consultant not to undertake physical activity for health reasons

#### Healthcare professional eligibility criteria

Currently working as a HCP (e.g. physiotherapists, occupational therapists) delivering home/community based stroke rehabilitationCapacity and willingness to undertake intervention training, delivery and assessment throughout study durationAbility to deliver the intervention programme to up to five stroke survivors

### Sample size

We aim to recruit and retain up to 35 stroke survivors (in line with standard guidance for feasibility studies [26]). As this is a feasibility study, a formal sample size calculation has not been undertaken. The sample size has been selected to allow adequate testing of the intervention and has been based on local resources. We aim to recruit up to 12 HCPs to take part in the training programme and intervention delivery. This sample size has been decided upon based on feedback from study sites.

### Case ascertainment recruitment and consent

#### Stroke survivors

Eligible stroke survivors will be identified by a HCP or a clinical trials officer (CTO) who will explain the nature of the study and provide the stroke survivor/informal carer with an information sheet. After allowing sufficient time for this information to be considered, and an opportunity to ask questions, informed written consent will be obtained from the stroke survivor. Where a stroke survivor is able to provide consent but is unable to sign the consent form (e.g. because of weakness of the dominant hand following stroke), consent will be confirmed orally in the presence of a witness (an individual not otherwise involved in the study) who will sign the consent form on behalf of the stroke survivor.

The original consent forms will be retained at the study sites, and a copy will be given to the stroke survivors. A copy of each stroke survivors’ consent form will be filed in their medical notes at the study sites.

Due to the nature of this study and its small size, we plan for the information sheet and consent form to be available only in English. However, interpreters and translation of written material will be considered should a potentially eligible stroke survivor require this support to participate.

